## Abstract

**Introduction:**

Metacarpal shaft fractures (MSF) are common traumatic hand injuries that usually affect young people of working age. They place a significant burden on healthcare resources and society; however, there is a lack of evidence to guide their treatment. Identifying the most beneficial and cost-efficient treatment will ensure optimisation of care and provide economic value for the National Health Service. The aim of this study is to assess the feasibility of a randomised controlled trial comparing surgical and non-surgical treatment for MSF in adults.

**Methods and analysis:**

This is a multicentre prospective cohort study, with a nested qualitative study consisting of patient interviews and focus groups, and an embedded factorial randomised substudy evaluating the use of text messages to maximise data collection and participant retention. The outcomes of interest include eligibility, recruitment and retention rates, completion of follow-up, evaluation of primary outcome measures, calculation of the minimal clinically important difference (MCID) for selected outcome measures and establishing the feasibility of data collection methods and appropriate time-points for use in a future trial. Data will be captured using a secure online data management system. Data analyses will be descriptive and a thematic inductive analysis will be used for qualitative data. Minimum clinically important effects for each patient-reported outcome measure will be estimated using anchor-based responsiveness statistics and distribution-based methods.

**Ethics and dissemination:**

This study has received ethical approval from the Research Ethics Committee and the Health Research Authority (REC reference 20/EE/0124). Results will be made available to patients, clinicians, researchers and the funder via peer-reviewed publications and conference presentations. Social media platforms, local media and feedback from the Patient Advisory Group will be used to maximise circulation of findings to patients and the public.

**Trial registration number:**

ISRCTN13922779.

Strengths and limitations of this studyProvides comprehensive information to inform the design and implementation of a future trial comparing treatments for metacarpal shaft fractures (MSF), including evaluation of multiple outcome measures and calculation of minimal clinically important difference to inform future sample size calculations.Provides complementary person-centred insight into MSF and research design, conduct and delivery through embedded qualitative assessments.Evaluates effective text message strategies for maximising data collection and retention in research studies.A detailed cost evaluation is a particular strength of the study and will deliver a comprehensive analysis of the costs of treatments available for MSF.Limited assessment of randomisation.

## Introduction

Metacarpal shaft fractures (MSF) are common traumatic hand injuries reported to represent 18%–31% of hand fractures.^1–4^ They usually affect young adult males, often in the third decade of life,^1 5^ with the fourth and fifth metacarpal most commonly injured.^1–6^

In 2016, there were 23.5 million accident and emergency (A&E) department attendances in the UK with fractures being the second most common reason for presentation.^7^ As hand fractures make up 25% of all A&E attendances^8^ and MSF comprise 18%–31% of hand fractures,^1–4^ MSF therefore place a significant burden on healthcare resources.

MSF predominantly affect those of working age^2–4 8 9^ and are thus associated with significant cumulative morbidity.^10^ Missed time off work significantly increases the economic burden of MSF.^10^ However, there is no UK-specific data on the healthcare-associated costs, socioeconomic, or societal costs of these injuries.

There is wide variability in the management of MSF. MSF can be managed non-surgically with appropriate reduction and immobilisation,^11 12^ or surgically using a variety of different techniques, including Kirschner-wires (K-wires), intraosseous wires, interfragmentary compression screws, plates or external fixators.^13^

A systematic review undertaken in 2019 of treatment interventions for MSF identified 699 records and no randomised controlled trials (RCTs) comparing surgical to non-surgical treatments.^14^ The only retrospective cohort study had several key limitations including small patient numbers, low follow-up rate (17%) and lack of use of a patient-reported outcome measure (PROM) validated in MSF.^15^ A search of the WHO ISCTRP portal also revealed no ongoing or registered trials worldwide.^14^

### Rationale for study

There is a lack of good quality, large comparative trials to guide the treatment of MSF. There are no published or ongoing RCTs or cohort studies comparing surgical versus non-surgical treatment for MSF. In addition, though the use of PROMs in both the clinical and research setting has increased in recent years, there is no evidence of reliability, validity and responsiveness of PROMs in MSF.

There are several gaps in the literature:

No consensus on acceptable parameters of deformity or displacement, leading to widespread variation in treatmentNo core outcome sets for hand trauma, so we do not know which outcome measures are best suited for the study of MSFNo qualitative data exploring patient experience of MSF and their treatmentNo evaluation of the cost-effectiveness of treatment modalities for MSFNo high-quality published evidence comparing treatment modalities for MSF

The lack of existing evidence supports the need for a well-designed, pragmatic, multicentre RCT to identify the most beneficial and cost-efficient treatment for MSF in adults. This study aims to assess the feasibility, acceptability and practicality of such a trial by providing information about study design, number of eligible patients, recruitment, completion of follow-up, selection of appropriate outcome measures, assessment of minimal clinically important difference (MCID) for selected outcome measures, costs of treatments and measures to optimise recruitment, engagement and retention in a future trial.

### Study objectives and purpose

The overall purpose of this study is:

To investigate the feasibility and acceptability of conducting a multicentre RCT to assess the clinical and cost-effectiveness of surgical and non-surgical treatment for MSF in adults.To provide complementary, detailed and person-centred insight that will inform RCT design through the identification of barriers to participation among patients with MSF, and to develop novel solutions to engage these cohorts in research.

The objectives of the study (table 1) were developed at a MSF Consensus Workshop, held by the Centre for Evidence Based Hand Surgery in Nottingham, November 2018 involving patients, clinicians, therapists and clinical trials methodologists.^16^

**Table 1 T1:** Study objectives

How objective will inform the definitive trial	Objective
Recruitment for a future trial	Define eligibility criteria for the future trial, which correctly identify appropriate patients for whom a treatment decision is suitable Estimate the proportion of referred NHS patients who meet these eligibility criteria Assess recruitment and retention rates
Outcomes for use in a future trial	Evaluate outcomes for use as primary and secondary outcomes Calculate minimal clinically important difference for the proposed primary outcome measure Investigate feasibility of collecting outcome data frequently, in order to capture subtle improvements in patient-assessed or clinician-assessed outcomes
Follow-up	Estimate follow-up and outcome completion rates for both clinic and remotely assessed outcomes Explore optimum time-points for follow-up
Sample size calculation	Estimate the sample size required for a definitive study
Use of remote assessments in a future trial	Evaluate the utility and acceptability of remote completion of health resource use questionnaires to assess the impact of care on health service use and productivity Evaluate the utility and acceptability of remote, electronically administered patient assessments
Economic assessment	Inform the design of a future cost-effectiveness analysis by exploring the costs of treatment modalities through capture of NHS resource use and representative micro-costing
Patient-centred insight into research design, conduct and delivery	To explore participant experience of MSF, treatment and recovery To explore participant experience of research processes and study burden associated with outcome measures To gain recommendations on future study design and mechanisms to facilitate study delivery
Facilitate engagement and retention among patients with MSF in a future trial	To explore the use of health technology applications and social media in optimising participation and engagement in research

MSF, metacarpal shaft fractures; NHS, National Health Service.

## Methods and analysis

### Study configuration

FACTS is an observational, multicentre, prospective cohort study. Treatments will not be randomly allocated; patient care will be determined in the usual way as per the treating clinician.

Patients who meet the eligibility criteria (table 2) will be recruited from hand fracture clinics at participating National Health Service (NHS) hospitals. Where participants have multiple MSF with potentially variable fracture patterns, a single digit will be selected as the ‘study finger’. Participants with additional hand or upper limb injuries will be included and the latter recorded. Written informed consent will be obtained from all participants by an appropriately trained research associate prior to entering the study. Thereafter, participants will be reviewed in a face-to-face clinic visit at 6 weeks and remotely at 3 and 6 months. This was supported by previous studies of MSF reporting full range of motion in almost all patients by 6 months.^17^ Furthermore, previous studies in similar patient cohorts with follow-up of 12 months or longer suffered high drop-rates or struggled to recruit adequate numbers of participants. A participant pathway flowchart is illustrated in figure 1.

**Table 2 T2:** Eligibility criteria

Inclusion criteria	Adults 16 years or older Radiologically confirmed metacarpal shaft fracture Acute metacarpal shaft fracture affecting the index to little finger(s), presenting within 10 days of injury Willing and able to give informed consent Ability to understand English
Exclusion criteria	Fracture(s) of the thumb Fractures extending into the joint surface Fracture(s) of the metaphyseal base and/or neck of the metacarpal Fracture(s) associated with dislocation at the carpometacarpal joint or other adjacent joint dislocation Open fractures Undisplaced fractures, defined as those with a visible fracture line on radiographs but anatomical alignment, that is, the bone fragments remain aligned with no evidence of movement of the fracture fragments on anteroposterior, lateral or oblique radiographs Patients who would not be able to adhere to study procedures or complete the study questionnaires

**Figure 1 F1:**
[figure not shown]
Study flow diagram. MSF, metacarpal shaft fractures. SMS, Short Message Service.

A nested qualitative study consisting of two elements, patient interviews and focus groups, will be conducted to provide patient-centred insight into study procedures and explore the individual impact of the injury. Participants will be selected from the prospective cohort study, using purposive sampling that prioritises young males, and further written informed consent separately sought for this element of the study.

A detailed cost evaluation to establish the costs of treatments for MSF through representative micro-costing will be undertaken. Resource use directly linked to the MSF and its sequela and/or complications over the 6 months of follow-up will be recorded for each participant. Unit cost data will be obtained from national databases such as NHS reference costs, the British National Formulary (BNF) and Personal Social Services Research Unit (PSSRU) Costs of Health and Social Care.^18^

A two by two by two factorial randomised substudy will be nested within the main cohort study. Once participants have consented to the cohort study or qualitative study, they will be randomised to the following interventions to evaluate the use of text messages in maximising data collection and participant retention; frequency of text messages—either fortnightly or monthly; two-way communication—text message requiring a response from the participant versus a notification message only; and personalisation—a personalised message versus a standard automated message.

### Treatment groups

Participants will enter a group according to their primary mode of treatment on enrolment into the study. Patients will undergo standard care as per their treating clinician. This will be decided by their clinical care team and will not be affected by their involvement in the study. Treatment groups will be defined as follows;

Surgery: any surgical treatment, defined as insertion of metal via an open or percutaneous approach in an operating theatre, such as open reduction internal fixation, closed reduction internal fixation, intramedullary fixation or wiring, extramedullary wiring or external fixation.

Non-surgical treatment: any ‘non-surgical’ treatment, defined as regimens with or without reduction (partial or complete) of the fracture, any type of splinting or cast, and/or immediate or delayed mobilisation delivered in a clinic or therapy room environment.

### Outcomes

Participants will be invited to attend a research clinic at 6 weeks following injury. During this visit, clinical assessments of their hand including range of movement, grip strength and presence of rotational deformity or extensor lag will be recorded. Radiographs taken as part of routine clinical care will also be reviewed. The location, fracture morphology, amount of shortening, angulation and presence of step-off deformity on initial radiographs at presentation will be recorded. Complications will be identified by review of the patients’ healthcare records at 6 weeks, 3 months and 6 months. Cosmesis will be assessed from question 10 of the Patient Evaluation Measure (PEM), at 6 weeks, 3 months and 6 months. Participant-reported complications will be recorded at the 6-week research clinic visit.

The following PROMs were selected for use following discussions between clinicians, patients, therapists and researchers at the MSF consensus workshop.^16^ They were prioritised due to their ease of use and validity and will be collected at baseline, 6 weeks, 3 months and 6 months.

#### Patient Evaluation Measure

The PEM consists of 11 items relating to hand function and appearance, each scored from one to seven from best/normal to worst. It is the PROM of choice in the British Society for Surgery of the Hand (BSSH) National UK Hand Registry (www.ukhr.net) and has been demonstrated to be reliable, valid and responsive for assessing hand disorders.^19 20^

#### Patient-reported outcomes measurement information system upper extremity

The PROMIS UE (PROMIS UE Item Bank V.2.0) is a computerised adaptive test, developed by the United States National Institute of Health using item response theory. It has been validated in upper limb fracture and is designed to minimise patient burden and theorised to measure latent traits more precisely than existing PROMs.^21^ For participants who do not engage with electronic means, a paper-based short-form alternative version is available.

#### Shortened Disabilities of the Arm, Shoulder and Hand Outcome Measure (QuickDASH)

The Disabilities of the Arm, Shoulder and Hand Score (DASH) is the most commonly used PROM in hand and wrist trauma and has consistently demonstrated good reliability, validity and responsiveness in several psychometric studies.^22^ It consists of 11 items, developed from the original 30-item DASH to improve practicality and eliminate item redundancy.^23^

#### European Quality of Life Questionnaire (EQ-5D-5L)

The EQ-5D-5L is a validated, generalised and standardised instrument comprising a Visual Analogue Scale (VAS) measuring self-rated health and a health status instrument, consisting of a five-level response for five domains related to daily activities.^24^ This standardised measure of health status provides a simple, generic measure of health for clinical and economic appraisal.^25^

#### Global Rating of change (GROC)

The GROC scale is commonly used as an anchor when calculating MCID. It is designed to quantify a patient’s improvement or deterioration over time, thus providing a means of measuring self-perceived change in health status.^26^ A 7-point scale ranging from −3 (very much worse) to +3 (very much better), with 0 indicating ‘unchanged’, will be used.

### Sample size and Justification

As this is a feasibility study, formal sample size calculations for between-group comparisons are not appropriate. However, we will seek to include as many as 84 participants in the study, aiming for comparable numbers in each treatment group. This sample size will enable estimation of recruitment fraction with margin of error (half width of 95% CI) of <9 percentage points and of proportions estimated from the recruited sample, such as completeness of follow-up, to within 13 percentage points.

A purposive sample of 12–16 participants, who indicate a willingness to be interviewed and/or attend focus groups, will be recruited to the qualitative study. Participants who decline to participate in the main cohort study will also be invited for interview.

### Analysis of outcomes

The outcomes of interest include feasibility outcomes relating to; assessment of eligibility, recruitment and retention rates; completion of follow-up; evaluation of outcome measures and calculation of the MCID for selected outcome measures using quantitative and qualitative assessments; and establishing the feasibility of data collection methods and appropriate time-points for use in a future trial. To address these feasibility aims, data analyses will primarily be descriptive with 95% CIs to quantify uncertainty in estimates where appropriate.

### MCID evaluation

Minimum clinically important differences for each PROM at 3 months will be estimated using three anchor-based responsiveness statistics: (1) standardised response mean; (2) effect size and (3) Guyatt’s Responsiveness Index. An estimation of the MCID will also be calculated by distribution-based methods, using the SE of measurement, SD and effect size. The minimal detectable change will also be calculated to ensure the MCID is greater than the measurement error of the PROM. The sensitivity and specificity of the PROM will be assessed in conjunction with the MCID, as calculated above.

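### The anchor-based MCID is fixed at 3 months while the future trial's time-point is still open, so choosing 6 weeks or 6 months would leave no matching anchor-based MCID

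*Protocol article*

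**What the plan says.** The first sentence under MCID evaluation sets the visit: "Minimum clinically important differences for each PROM at 3 months will be estimated using three anchor-based responsiveness statistics". It names the standardised response mean, the effect size and Guyatt's Responsiveness Index. The next sentence has no time-point: "An estimation of the MCID will also be calculated by distribution-based methods, using the SE of measurement, SD and effect size".

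Other parts of the article treat the future trial's timing as something still to be found. Table 1, in the Follow-up row, lists "Explore optimum time-points for follow-up". Analysis of outcomes repeats the aim as "establishing the feasibility of data collection methods and appropriate time-points for use in a future trial".

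Table 1 also sets the objective "Estimate the sample size required for a definitive study", and the strengths and limitations list gives the purpose of the MCID work as "calculation of minimal clinically important difference to inform future sample size calculations".

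Under Outcomes, the PROMs "will be collected at baseline, 6 weeks, 3 months and 6 months". The GROC scale appears in the list under that statement, with the remark "The GROC scale is commonly used as an anchor when calculating MCID". Its own entry gives no separate schedule.

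**The concern.** The visit for the definitive trial is to be an output of this study, yet one of the main inputs to that trial's sample size is fixed beforehand at one of three candidate visits. If the feasibility evidence points to 6 weeks or 6 months, the team would have to carry the 3-month anchor-based MCID over to a different stage of recovery, or do without one.

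There is reason to doubt that the value carries over unchanged. All three named statistics are built on change in score up to the visit concerned, so they depend on which visit that is. The Study configuration section itself cites earlier work in which nearly all patients had regained full movement by 6 months, which implies that patients are at different stages at the three visits. At stake is how well the study can meet its own objective of sizing the definitive trial.

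**Working it through.** **The plan's own figures.** The article gives no MCID, SD, alpha or power, so there is no figure on this point to reproduce. Its only numerical design statements are the precision bounds under Sample size and Justification. With 84 participants and a proportion of 0.5, the 95% half-width is 1.96 × √(0.5 × 0.5 / 84) = 10.7 percentage points, inside the stated 13. For the recruitment fraction, trying values from 0.4 to 0.8 with 84/fraction people approached gives at most about 8.2 points, inside the stated 9. Both bounds hold, and neither bears on this point.

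**The text side by side.**

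| Element | Time-point in the article |
|---|---|
| Anchor-based MCID | 3 months |
| Distribution-based MCID | none stated |
| Minimal detectable change, sensitivity and specificity | none stated |
| Descriptive analyses with 95% CIs | general, not tied to a visit |
| PROM collection | baseline, 6 weeks, 3 months, 6 months |
| GROC collection | inferred from its place in the same list |
| Future trial's time-point | open, an objective of the study |

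The anchor-based MCID is the only element tied to a single visit. For 6 weeks and 6 months, then, the plan can supply an SD and possibly a distribution-based MCID, but as written no anchor-based one.

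**What a different MCID would do to the sample size (illustration).** Assumptions: comparison of two means, 1:1 allocation, two-sided alpha 0.05, SD held fixed.

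n per arm = 2 × (z for alpha + z for power)² × (SD/MCID)²

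N is therefore proportional to 1/MCID². If the MCID at the chosen visit is k times the 3-month value, N is multiplied by 1/k²:

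- k = 0.8: 1/0.64 = 1.56
- k = 0.9: 1/0.81 = 1.23
- k = 1.1: 1/1.21 = 0.83
- k = 1.2: 1/1.44 = 0.69

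As an example, take a 3-month MCID/SD ratio of 0.5 and 90% power: 2 × (1.96 + 1.28)² / 0.25 gives 85 per arm after rounding up. With the MCID 20% lower (ratio 0.4) it is 132 per arm; with the MCID 20% higher (ratio 0.6) it is 59 per arm.

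**The case against.** The best case against the point is that fixing one visit in advance is legitimate. An intermediate visit is a sensible choice when recovery is nearly complete by 6 months, and a condensed article may leave further visits to the full protocol or analysis plan. The second part would settle the matter if the article were silent. It is not silent: it states a visit, gives no reason for it, and leaves the future time-point open. The first part stands as a reason to keep 3 months, not as a reason to stop there.

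Three stronger readings are tempting and should not be adopted.

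- A reader might infer that there would be no SD for 6 weeks or 6 months either. The article does not say so. The PROMs are collected at each visit, descriptive analysis is planned generally, and nothing limits SDs to 3 months. A calculation that carries a 3-month SD to another visit would therefore measure something the plan does not prescribe.
- A reader might infer that all the MCID work is confined to 3 months. Only the anchor-based sentence names that visit. Even there other visits are not expressly excluded, although 3 months alone is the ordinary reading.
- A reader might infer that the time-point objective cannot be met, because responsiveness at one visit cannot rank the visits. The article does not make responsiveness the criterion. Table 1 places the time-point objective beside completion rates, and the patient and public involvement section shows timing being shaped by patient discussions.

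Two cautions also stand. That GROC is collected at 6 weeks and 6 months is inferred from its position in the list; the same sentence includes baseline, where a rating of change has no meaning, so the schedule should be confirmed. And choosing the visit by comparing noisy estimates, then taking the MCID and SD from the winner, would use the same data for selection and estimation.

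**Conclusion.** The point holds for the anchor-based MCID and no further. The plan ties that estimate to 3 months without a reason, while leaving the future trial's time-point open and intending the MCID to inform the sample size. If 6 weeks or 6 months is chosen, no matching anchor-based MCID is planned.

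The size is conditional. It arises only if another visit is chosen and the MCID differs there; if the MCID is the same at all visits, the 3-month value can be combined with the SD of the chosen visit and nothing is lost. A 20% difference in the MCID at a fixed SD would change the required number by a factor of about 1.56 or 0.69, but that 20% is an assumption and not a figure from the article. This is an inexpensive improvement, not a defect that invalidates the study.

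**What to change.** In the MCID evaluation section, keep the 3-month analysis and add the same anchor-based MCID and responsiveness analysis for each PROM at 6 weeks and 6 months, each with its 95% CI. Confirm there that GROC is recorded at all three follow-up visits, and give the time-point or time-points for the distribution-based estimates.

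State that the definitive sample size will use the MCID and SD from the visit chosen on all the feasibility evidence: completion, descriptive and qualitative data, with responsiveness as one input and not the sole criterion.

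The cost is two repeats of a planned analysis. If GROC is scheduled as its place in the list suggests, no extra visits, questionnaires or participants are needed. The downside is imprecision: the estimates come from at most 84 participants, and some visits may have few stable or unchanged patients, which weakens Guyatt's index in particular. The confidence intervals should be reported so that this is visible when the trial is sized.

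### The check of the MCID against the minimal detectable change does not say which MCID is tested; for SEM-, SD- and effect-size-based values it cannot show whether a change that matters to patients exceeds measurement error

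*Protocol article*

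**What the plan says.** The MCID evaluation section of the protocol article plans two families of estimate. The first is labelled anchor-based: "Minimum clinically important differences for each PROM at 3 months will be estimated using three anchor-based responsiveness statistics". The three statistics are the standardised response mean, the effect size and Guyatt's Responsiveness Index. The second is distribution-based: "An estimation of the MCID will also be calculated by distribution-based methods, using the SE of measurement, SD and effect size". The check follows at once: "The minimal detectable change will also be calculated to ensure the MCID is greater than the measurement error of the PROM". The section ends with a further assessment: "The sensitivity and specificity of the PROM will be assessed in conjunction with the MCID, as calculated above".

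The external anchor is described in the section on the Global Rating of Change: "The GROC scale is commonly used as an anchor when calculating MCID". It has seven points, from −3 to +3, with 0 for no change. The MCID evaluation section does not mention it. The abstract repeats that MCIDs "will be estimated using anchor-based responsiveness statistics and distribution-based methods". Table 1 gives the purpose, "Calculate minimal clinically important difference for the proposed primary outcome measure", and separately lists estimating the sample size of the definitive study as an objective.

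The article states no SEM multiplier, SD fraction, reliability coefficient or confidence level for the MDC.

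**The concern.** Comparing an MCID with the MDC is meant to show that the smallest change patients care about is larger than the noise of the instrument. That requires the two sides to come from different information: one from what patients report, the other from measurement error. A distribution-based MCID comes from the same SEM or SD as the MDC. Set against each other, the two share terms that cancel, and no patient-perceived change is left in the comparison.

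At stake are two uses that the study is designed to serve: choosing outcome measures for the definitive trial and setting its sample size. Required sample size varies with one over the square of the target difference. If the target moved from 1 SEM up to the MDC95 only so that the check would no longer fail, the required number would fall by a factor of about 2.772² ≈ 7.7, with no patient information behind the change.

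**Working it through.** There is no figure in the article to reproduce, so the check is worked algebraically.

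**Assumed inputs (standard definitions, not given in the article).** SEM = SD × √(1 − r), where r is reliability. MDC = z × √2 × SEM. At 95% this is 1.96 × 1.414 × SEM = 2.772 SEM. At 90% it is 2.326 SEM.

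**Step 1. MCID = k × SEM.** The condition k × SEM > 2.772 × SEM reduces to k > 2.772. Both SD and r cancel.

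| MCID | MCID/MDC95 | MCID/MDC90 |
|---|---|---|
| 1 SEM | 0.361 | 0.430 |
| 1.96 SEM | 0.707 | 0.843 |

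Both fail for every PROM. Any other k also gives an answer known before data collection.

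**Step 2. MCID = c × SD (an SD fraction or effect-size benchmark).** The condition c × SD > 2.772 × SD × √(1 − r) reduces to r > 1 − (c/2.772)². SD cancels and r stays.

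| MCID | passes MDC95 only if r > | passes MDC90 only if r > |
|---|---|---|
| 0.2 SD | 0.995 | 0.993 |
| 0.5 SD | 0.967 | 0.954 |
| 0.8 SD | 0.917 | 0.882 |

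For 0.5 SD the ratio to MDC95 is 0.40 at r = 0.80, 0.57 at 0.90, 0.81 at 0.95 and 1.04 at 0.97. This version does respond to data, but only through reliability.

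**Step 3. MCID = mean change in a GROC-defined group, equal to a × SD.** The ratio is a / (2.772 × √(1 − r)). The form matches Step 2, but a is now observed in patients who reported a change and is not a chosen constant. Illustrative values against MDC95, with a and r assumed:

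| a | r = 0.80 | r = 0.90 | r = 0.95 |
|---|---|---|---|
| 0.3 | 0.24 | 0.34 | 0.48 |
| 0.8 | 0.65 | 0.91 | 1.29 |
| 1.0 | 0.81 | 1.14 | 1.61 |
| 1.2 | 0.97 | 1.37 | 1.94 |

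Take two PROMs that both have r = 0.90, with anchored changes of 0.8 and 1.0 SD. The anchored check separates them (0.91 and 1.14). The 0.5 SD check gives 0.57 for both, and the 1 SEM check 0.361 for both.

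**Step 4. Does the section supply the quantity used in Step 3?** The standardised response mean, the effect size and Guyatt's index each divide a change by an SD. They have no units, whereas the MDC is in PROM score points. A conversion, or a GROC-defined mean change in score points, would be needed, and the section states neither.

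**The case against.** The strongest reply is that the anchor-based family comes first in the section, the distribution-based one is an addition, and GROC is collected for this purpose. On that reading the MCID being checked is the anchored one, the comparison is the usual one, and Step 3 shows that it is informative. The multipliers, the MDC level and the choice of estimate may also be settled in a full protocol or analysis plan that is not shown.

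Part of this stands. Missing multipliers are not a fault in a condensed article, and none is claimed here. But supplying them would not cure Step 1, because every k gives a predetermined answer. The anchored reading also lacks a stated score-point quantity, because the three named statistics are unitless.

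A reader might infer more than the documents support, in three ways:

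- *That the check as a whole is fixed by the multipliers and cannot separate a usable PROM from an unusable one.* This is exact only for SEM-based values. For SD- and effect-size-based values r remains, is estimated from data, and can rank PROMs by reliability.
- *That every PROM would be rejected.* A 0.5 SD MCID passes once r exceeds about 0.967, and the article does not say that a PROM failing the check is dropped.
- *That outcome choice and the target difference would rest on a constant.* The article does not say that a distribution-based value alone sets the sample size. It also plans sensitivity and specificity, and qualitative as well as quantitative assessment of the outcome measures.

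**Conclusion.** The point holds in a limited form. The section tests an unspecified MCID against the MDC. Under the standard definitions, the result for an SEM-based MCID is decided by the multiplier alone: 1 SEM and 1.96 SEM reach 36% and 71% of MDC95 and always fail. For an SD- or effect-size-based MCID the check is a reliability threshold, about 0.967 for 0.5 SD and 0.917 for 0.8 SD. Neither says whether a change of importance to patients exceeds measurement error. The only family that could answer that is specified through unitless indices.

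The cancellation in the SEM case needs only that the MDC is a multiple of the SEM. The numerical thresholds rest on the assumed definitions and multipliers, and using MDC90 lowers them without changing the conclusion. Because the MCID is a stated deliverable for the definitive trial, the wording should be corrected, but the defect is confined to this check and does not undermine the study.

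**What to change.** Amend the MCID evaluation section in one or two sentences, to this effect:

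- The MDC will be compared with a GROC-anchored MCID in PROM score points, for example the mean 3-month change among participants who rate themselves minimally improved. This will be reported with its 95% CI beside the MDC.
- SEM-, SD- and effect-size-based values will be reported as supporting description. They will not be tested against the MDC, and will not be used alone as the target difference for the definitive trial.

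The GROC and the PROM scores are already planned at 3 months, so no new data are needed. The cost is precision. The study aims for up to 84 participants ("we will seek to include as many as 84 participants in the study"), and those in one GROC category may be few. The interval may then be wide and the comparison unresolved for some PROMs, which should be reported as such. No formal pass rule on the lower confidence limit is required.
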